**APPENDIX B**

**LEAP Intervention Interview Schedule**

# Topic Guide: LEAP participants (early participation)

**Participation in the trial**

1. How did you come to be involved in this research? (explore recruitment pathway, materials etc.).
2. Why did you agree to take part in the study (what was attractive/interesting)?
3. What are your expectations for the study? (what do you hope to get from it?).
4. How have you found being in the study so far (what has surprised you/been as expected?).
5. How do you feel about having been chosen by chance to get access LEAP? (explore concept of randomisation – do participants understand it)?

**Experience with LEAP**

Function

1. What are your general impressions of LEAP?
   1. What did you think of LEAP when you first saw it?
2. Talk me through how you have used LEAP so far (use site map document to support discussion about pathway through website)
   1. What are the reasons for using particular modules and tools but not others?
   2. What is useful about each module and tool, and what is not useful? (what could be improved?)
   3. What problems did you have in using LEAP?
   4. What worked well?
   5. Have you used any other sources of information outside LEAP? (e.g. other websites)

1. What was your experience of the following features (did they make sense, were they useful?):
   1. Dashboard?
   2. Diary (i.e. activity planner)?
   3. Notifications and prompts?
   4. The mentor?

*Concept & expectation*

1. In what ways has LEAP been what you expected?
   1. How has it been different?
2. What do you expect will happen at the end of the study:
   1. To how you live? (will LEAP change your behaviour)?
   2. To your use of LEAP (would you continue to use it if it was available)?
3. Would you recommend LEAP to another person (if so why)?
   1. Have you shared your log-in details with anyone else?
4. Is there anything important we haven’t discussed about your experience of LEAP?

**Experience with HAP**

You took part in some measures of your health (HAP).

1. What was your experience of:
   1. Time taken
   2. The number/range of measures (did it feel comprehensive or too much)?
   3. What was difficult to do (if anything)
2. If you didn’t have the measures, would you have used LEAP differently?

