### Domain 3: Acceptability and use of HAP battery

1. How do participants’ experience the HAP assessment overall (e.g. time taken, impression of question type, format and delivery)?
2. What components/instruments of the HAP measures were acceptable, and which were difficult to complete (e.g. difficult to understand, repetitive, or ‘simplistic’)?
3. What (if anything) is missing from the HAP in terms of measuring health and wellbeing *in the retirement transition*?

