## Data collection and analysis

Qualitative data will be collected through individual semi-structured interviews which will take place at the participants’ home or at a nearby location suitable for them. The scope and depth of the interviews will vary across groups. Participants drawn from the groups receiving the LEAP intervention will take part in an interview lasting up to 60 minutes. The interview schedule for this group is presented in Appendix B. Participants in the control condition will take part in an interview of up to 40 minutes duration. The interview schedule for this group is presented in Appendix C. Participants who initially declined to take part in the pilot, or those who withdrew from the pilot will take part in a brief interview of up to 20 minutes duration. Interview schedules for these groups are presented in Appendices D and E respectively.

We will conduct a thematic analysis (Guest etal., 2012) of the data using a coding manual developed by two of the research team (SM, BH) through preliminary analysis of data and the research questions and objectives. Data will be organised using a software package (NVivo).

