**Dietary intake**

Dietary intake will be assessed using the multiple pass 24-hour recall method. In order to assess usual food intake, before and after interventions participants will be asked to complete a 24-hour dietary recall on three days, including two weekdays and one weekend day. In order to reduce possible effects of between-day variability in food intake, participants will be required to complete these dietary recalls on the same days of the week at each timepoint (eg Thursday, Friday, and Saturday; or Sunday, Monday, and Tuesday). An online diet questionnaire, the Oxford WebQ (Liu et al 2011), will be used. The Oxford webQ questionnaire takes around 15 to 20 minutes to complete. The Oxford WebQ is self-administered and assesses what participants ate and drank the previous day.

Five ageing-related domains will be will be evaluated in this study, physiological and metabolic health, physical capability, cognitive function, psychological wellbeing, and social wellbeing. The procedure for administration of the Health Ageing Phenotype (HAP) is explained in the HAP administration guidelines (appendix Z).

1. Physiological and Metabolic Health Domain

a) Blood pressure. Resting blood pressure will be measured in triplicate using a manual BP monitor. Before the measurement participants will be invited to rest in a sitting position for at least 10 minutes. An appropriate cuff size will be used for the measurement of each subject which will be used for all other measurements of BP.

b) Forced expiratory volume (FEV1). FEV1 will be assessed before and after interventions with a portable handheld spirometer (Micro 1). Briefly the participant will take in as deep breath as possible, when full place the mouthpiece in his/her mouth. Close his/her lips tightly around the mouthpiece. Blow through the mouthpiece into the spirometer, blowing air out as hard, fast, smoothly and completely as possible. Record the FEV1 from at least two and up to five technically satisfactory manoeuvres.

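### No topic guide asks what the HAP battery leaves out, although the protocol lists this as a research question, and the nearest prompt is one-sided

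*Protocol*

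**What the plan says.** Under Qualitative Assessment, Domain 3 (acceptability and use of the HAP battery) lists three questions. The third is "What (if anything) is missing from the HAP in terms of measuring health and wellbeing", specifically for people in the retirement transition.

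The guides for trial participants are printed in full: Appendix B (LEAP, early and late) and Appendix C (control, early and late). Each ends with the same short block, Experience with HAP, introduced by "You took part in some measures of your health (HAP". The block asks for the participant's experience of three things and then adds one further question:

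- the time taken;
- "The number/range of measures (did it feel comprehensive or too much";
- "What was difficult to do (if anything";
- "If you didn’t have the measures, would you have used LEAP differently".

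On format, the section Data collection and analysis says "Qualitative data will be collected through individual semi-structured interviews".

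**The concern.** A stated research question should have at least one prompt that elicits an answer to it. Here the question on content gaps has none. The one prompt that touches on the breadth of the battery names two reactions, and both take the content to be at least sufficient. A participant who thinks something important was left out has to raise it unprompted.

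The question is not an idle one in this pilot. Appendix A names five HAP domains: "physiological and metabolic health, physical capability, cognitive function, psychological wellbeing, and social wellbeing". The descriptions of the Time and Changing Work modules report that the team's own qualitative work found time use, finances and the manner of leaving work to be important in retirement, and none of these is a named HAP domain. Appendix A also says that no suitable instrument was found for how meaningful and satisfying people find explicit social roles, so an untested questionnaire is used. This does not show that the battery has a gap. It does show why the team would want participants' views before fixing the battery for a definitive trial.

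**Working it through.** No sample size, power or error-rate figure is involved. The check sets the research question beside each place where it could be answered.

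**1. HAP block in the four trial-arm guides.** The block covers time, number and range, difficulty, and effect on use of LEAP. Guides carrying the number-and-range prompt in identical words: 4 of 4. Guides with an item on missing content: 0 of 4. Guides whose HAP block mentions retirement: 0 of 4.

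**2. Poles of the number-and-range prompt.** The poles offered are comprehensive (enough) and too much (more than enough). The pole not offered is too little, or something left out.

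**3. Closing catch-all questions.** In the LEAP guides the catch-all is "Is there anything important we haven’t discussed about your experience of LEAP". In the control guides the equivalent question concerns the website. In all four guides it comes before the HAP block, so it neither covers the HAP nor follows it.

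**4. Guides for people who declined or withdrew (Appendices D and E).** There is no HAP block, only a general closing question about taking part in the study.

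**5. Quantitative HAP questions (Compliance with HAP battery measurement procedures).** These cover completion time, the percentage completing, and the percentage of outcome data missing. Missing there means absent values, not absent content, so these data cannot answer Domain 3, item 3.

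**6. Interviews affected (Fig 3, all figures maxima).**

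- LEAP: 8 + 8 = 16
- Control: 4 + 4 = 8
- Trial-arm interviews using a guide with a HAP block: 16 + 8 = 24
- Reduced participation: 2 + 2 = 4
- All interviews: 24 + 4 = 28

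The omission therefore runs through up to 24 of up to 28 interviews. The other 4 or fewer use guides that do not mention the HAP. No other source of data on content gaps is described.

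**The case against.** The strongest reply is that these are guides for semi-structured interviews, not closed questionnaires. The stem asks openly about experience, and the bracketed words are a cue for the interviewer. A participant can answer that the battery was not comprehensive and say why, and the interviewer can follow up. Earlier items ask openly how the person has found being in the study. The coding manual is to draw on the research questions, so any gap that is volunteered should be coded. All of this stands, and it limits the point.

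A reader might go further than the document allows in several ways:

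- **That the wording leaves no room for a gap to be reported, or that the question gets no valid data.** Zero of four counts prompts, not answers. The open stem and the interview format allow some relevant data.
- **That the block asks about nothing but breadth.** It also covers time, difficulty and effect on use of LEAP.
- **That the judgement of whether the HAP measures are fit for purpose rests on this question.** The rationale section links that judgement to eligibility numbers and to recruitment, retention and completion rates.
- **That calling the battery measures of health steers answers towards the physical tests.** Nothing in the protocol shows this. Appendix A itself places a mental health scale within the psychological wellbeing domain.
- **That the difficulty prompt drops part of Domain 3, item 2.** That item gives repetitive and simplistic as examples of what makes a component difficult to complete, so the prompt follows its main term.
- **That the team would respond by shortening the battery.** The protocol says nothing of the kind.

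What the reply does not remove is that a listed question has no prompt, and that the nearest cue leans one way. Flexible interviewing may make up for this, but unevenly between interviewers and participants.

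**Conclusion.** The point holds as a minor mismatch between a stated question and its instrument. Domain 3, item 3 has no matching item in any of the four trial-arm guides, and the only related cue has no too-little side. With the guides used as printed, reports of missing content would be incidental, dependent on the interviewer and probably too few. If gaps are rarely mentioned, that could not be taken as evidence that participants found nothing missing, because most would not have been asked.

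This assumes that interviewers work from the printed guides without a further instruction to probe for gaps; the protocol describes none. Under-reporting is a judgement about one-sided cues, not a quantity that the document allows one to calculate. Randomisation, sample size and the quantitative feasibility outcomes are unaffected.

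**What to change.** Make the same two edits to the HAP block in all four guides (Appendix B early and late, Appendix C early and late):

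1. Replace the bracketed cue on number and range with a balanced one: *too few, about right or too many?*
2. Add one neutral open probe, for example: *Was anything important to your health or wellbeing around retirement not covered by these measures?*

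The cost is a wording change to one repeated block and, by estimate, a minute or so of interview time, against planned maxima of 60 minutes in the LEAP arm and 40 minutes in the control arm. If any interviews have already been held with the present wording, record which version each participant was given, so that silence on gaps in those transcripts is not counted as a negative answer.

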# Topic Guide: LEAP participants (late participation)

**Participation in the trial**

1. How did you come to be involved in this research? (explore recruitment pathway, materials etc.).
2. Why did you agree to take part in the study (what was attractive/interesting)?
3. What are your expectations for the study? (what do you hope to get from it?).
4. How have you found being in the study (what has surprised you/been as expected?).
5. Looking back - what factors helped you to stay to the end?
6. Were there any things that tempted to you leave the study? (was anything difficult or taxing?)
7. How did you feel about having been *chosen by chance* to get access LEAP? (explore concept of randomisation – do participants understand it)?

**Experience with LEAP**

*Function*

What are your general impressions of LEAP?

- 1. What did you think of LEAP when you first saw it?

1. Talk me through how you have used LEAP (use site map document to support discussion about pathway through website)
   1. What are the reasons for using particular modules and tools but not others?
   2. What is useful about each module and tool, and what is not useful? (what could be improved?)
   3. What problems did you have in using LEAP?
   4. What worked well?
   5. Did you use any other sources of information outside LEAP? (e.g. other websites)

1. What was your experience of the following features (did they make sense, were they useful?):
   1. Dashboard?
   2. Diary (i.e. activity planner)? – have participants continued to use this?
   3. Notifications and prompts?
   4. The mentor?

*Concept & expectation*

1. In what ways has LEAP been what you expected?
   1. How has it been different?
2. What do you expect will happen at the end of the study:
   1. To how you live? (will LEAP change your behaviour)?
   2. To your use of LEAP (would you continue to use it if it was available)?
3. Overall how would you describe LEAP (i.e., engaging, fun, boring, easy to use, intuitive, innovative etc.?)
   1. Would you recommend LEAP to another person (if so why)?
   2. Have you shared your log-in details with anyone else?
4. Is there anything important we haven’t discussed about your experience of LEAP?

**Experience with HAP**

You took part in some measures of your health (HAP).

1. What was your experience of:

a. Time taken

b. The number/range of measures (did it feel comprehensive or too much)?

c. What was difficult to do (if anything)

2. If you didn’t have the measures, would you have used LEAP differently?

**APPENDIX C**

**Control Group Interview Schedule**

**Topic Guide: NHS ‘LiveWell’ participants (early participation)**

**Participation in the trial**

1. How did you come to be involved in this research? (explore recruitment pathway, materials etc.).
2. Why did you agree to take part in the study (what was attractive/interesting)?
3. What are your expectations for the study? (what do you hope to get from it?).
4. How have you found being in the study so far (what has surprised you/been as expected?).
5. How do you feel about having been chosen by chance to get access the NHS LiveWell website? (explore concept of randomisation – do participants understand it)?

**Experience with NHS ‘LiveWell’ site**

Function

1. What are your general impressions of the NHS website?
   1. What did you think of website when you first saw it?
2. Talk me through how you have used the NHS ‘LiveWell’ site
   1. What parts of the site did you find most helpful? (which parts were least useful)?
3. In what ways has NHS ‘LiveWell’ been what you expected?
   1. How has it been different?
   2. Have you used any other sources of information outside LiveWell? (e.g. other websites)
4. What do you expect will happen at the end of the study:
   1. To how you live? (will the information gain from the website change your behaviour)?

b. To your use of the website (would you continue to use it if it was available)?

5. Would you recommend NHS LiveWell to another person (if so why)?

1. Is there anything important we haven’t discussed about your experience of the website?

**Experience with HAP**

You took part in some measures of your health (HAP).

1. What was your experience of:
   1. Time taken
   2. The number/range of measures (did it feel comprehensive or too much)?
   3. What was difficult to do (if anything)
2. If you didn’t have the measures, would you have used LEAP differently?

**Topic Guide: NHS ‘LiveWell’ participants (late participation)**

**Participation in the trial**

1. How did you come to be involved in this research? (explore recruitment pathway, materials etc.).
2. Why did you agree to take part in the study (what was attractive/interesting)?
3. What are your expectations for the study? (what do you hope to get from it?).
4. How have you found being in the study (what has surprised you/been as expected?).
5. Looking back - what factors helped you to stay to the end?
6. Were there any things that tempted to you leave the study? (Was anything difficult or taxing?)
7. How did you feel about having been *chosen by chance* to get access to the NHS LiveWell website? (explore concept of randomisation – do participants understand it)?

**Experience with NHS ‘LiveWell’ site**

Function

1. What are your general impressions of the NHS website?
   1. What did you think of website when you first saw it?
2. Talk me through how you have used the NHS ‘LiveWell’ site
   1. What parts of the site did you find most helpful? (which parts were least useful)?
3. In what ways has NHS ‘LiveWell’ been what you expected?
   1. How has it been different?
   2. Have you used any other sources of information outside LiveWell? (e.g. other websites)
4. What do you expect will happen at the end of the study:
   1. To how you live? (will the information gain from the website change your behaviour)?

b. To your use of the website (would you continue to use it if it was available)?

5. Would you recommend NHS LiveWell to another person (if so why)?

1. Is there anything important we haven’t discussed about your experience of the website?

**Experience with HAP**

You took part in some measures of your health (HAP).

1. What was your experience of:
   1. Time taken
   2. The number/range of measures (did it feel comprehensive or too much)?
   3. What was difficult to do (if anything)
2. If you didn’t have the measures, would you have used LEAP differently?

**APPENDIX D**

**Declined Participation Interview Schedule**

**TOPIC GUIDE: ‘NON-PARTICIPANTS’**

1. How did you come to be involved in this research? (explore recruitment pathway, materials etc.).
2. Why did you initially agree to take part in the study (what was attractive/interesting)?
3. What were your expectations for the study? (what do you hope to get from it?).
4. Please tell me how you came to leave the study? (explore reasons for leaving)
5. You’ve kindly agreed to this interview: what prompted you to take part in this discussion?
6. What factors might have encouraged you to stay in the trial had they been available at the time?
7. How did you feel about having been chosen by chance to [condition)?
8. Is there anything else we haven’t discussed about your participation in the study?

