### Domain 1: Participation in pilot

1. How did those participating in the pilot come to be recruited? (what did they think about the recruitment strategy, materials etc.)
2. What are the reasons for refusing to participate? (small sub-sample)
3. Why do people agree to take part in the study?
4. What do participants expect from the study? (Are their expectations met?)
5. What are the reasons for trial retention?
6. What are the reasons for trial attrition? (small sub-sample)
7. How do participants feel about being randomised to their arm of the trial (compare and contrast the different conditions)?
8. What are participants’ experiences of the diet, PA and social measures assessment at each time point? (e.g. acceptable? time needed to complete? ease of completion? etc)

Our research questions point to recruitment from 4 groups: 2 arms of the trial, participants who decline to take part in the pilot (e.g. decline to be randomised to a trial arm) but consent to the qualitative component, and participants who drop out of the pilot before the final assessment but consent to a qualitative follow up interview).

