## Recruitment and sampling

Semi-structured interviews will be conducted with a sample of participants in the trial from the intervention and control groups and two ‘reduced participation’ groups. The reduced participation groups will include people who initially declined to participate in the trial or to be randomised, but consented to a brief qualitative interview (n= up to 2), and people who withdraw from the trial but consent to a follow-up qualitative interview (n= up to 2), The number of participants interviewed from each group within the pilot trial is shown in Figure 3. In total therefore up to 28 participants will be included in the qualitative component of the pilot study, although the length of interview will vary by trial arm ranging from 60 to 20 minutes per interview. Interviews in the reduced participation groups may be considerably shorter (e.g. 10 minutes) in some instances.

|  | LEAP | Control | Reduced Participation |
| --- | --- | --- | --- |
| Participation stage: near baseline | (n≤ 8) | (n≤ 4) | Prior to randomisation: (n≤ 2) |
| Participation stage: near final assessment | (n≤ 8) | (n≤ 4) | Post randomisation: (n≤ 2) |
| Total: (n≤28) | **(n≤ 16)** | **(n≤ 8)** | **(n≤ 4)** |

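### The topic guide for people who declined repeats the withdrawal guide and has no item on why they declined; one item in each control guide asks about LEAP, which controls do not receive

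*Protocol*

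**What the plan says.** The objective under Qualitative Assessment covers reasons for taking part and for not taking part. Domain 1 turns this into two separate questions. Question 2 is "What are the reasons for refusing to participate? (small sub-sample" and question 6 is "What are the reasons for trial attrition? (small sub-sample".

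The Recruitment and sampling section under Qualitative Assessment defines a group for each question, with at most 2 interviews in each. The first group is "people who initially declined to participate in the trial or to be randomised", provided that they agree to a short interview. The second group is those who leave the trial after joining it and agree to be interviewed afterwards. Figure 3 places the first group before randomisation and the second after it. The Data collection and analysis section assigns them Appendices D and E respectively and allows each interview up to 20 minutes.

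Appendix D is headed as the schedule for those who declined. Two of its eight items are "Please tell me how you came to leave the study? (explore reasons for leaving" (item 4) and "How did you feel about having been chosen by chance to [condition" (item 7).

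Under Control Comparator, control participants are emailed a link to the NHS website and nothing else. In Appendix C, the HAP section of both the early and the late control guide nevertheless ends with "If you didn’t have the measures, would you have used LEAP differently".

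**The concern.** Two groups, two research questions and two appendices point to two different guides, but the text supplies only one. An interviewer who follows Appendix D would ask a person who never joined how they came to leave, what might have kept them in, and how they felt about a condition they were never given. The interviewer would not be prompted to ask why the person declined.

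Recruitment feasibility is a main purpose of this pilot, and these interviews are meant to show how recruitment could be improved. At most two short interviews are planned with people who declined, so there is little room to make up for a guide that points elsewhere.

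The control item is a smaller matter. A control participant cannot answer from experience a question about using LEAP.

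**Working it through.** No power, sample-size or alpha figure is involved. The check is an item-by-item comparison and a count.

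**Appendix D against Appendix E.** The headings differ (declined; withdrew), but the sub-heading is the same and 8 of 8 items are identical. Read for a person who declined before randomisation, the items fall out as follows:

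| Item | Subject | Fit |
| --- | --- | --- |
| 1 | How they came to hear of the research | Usable |
| 2 | Why they first agreed to take part | Largely presupposes agreement |
| 3 | What they expected of the study | Usable |
| 4 | How they came to leave | Presupposes having joined |
| 5 | Why they agreed to this interview | Usable |
| 6 | What might have kept them in the trial | Presupposes having joined |
| 7 | Feelings about the allocated condition | Presupposes allocation |
| 8 | Anything else about their participation | Usable as a closing prompt, though worded for participants |

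Three items (4, 6, 7) presuppose joining, leaving or allocation, and item 2 largely does. Items that ask why the person declined: 0 of 8. Item 7 is the clearest misfit, because for someone who was never randomised no condition exists to fill its bracket. The same eight items suit Appendix E, so the shared text is in substance the withdrawal guide.

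**Number of interviews with people who declined.** Figure 3 gives 16 (LEAP) + 8 (control) + 4 (reduced participation) = 28, which agrees with the stated total. People who declined account for at most 2 of these 28.

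**Control guides, top-level items.**
- Early guide: 5 (participation) + 6 (NHS website) + 2 (HAP) = 13. One item names LEAP, so 13 − 1 = 12 are unaffected.
- Late guide: 7 + 6 + 2 = 15. One item names LEAP, so 15 − 1 = 14 are unaffected.
- Interviews in which the item would be asked: at most 4 (early) + 4 (late) = 8.

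The affected item has the same wording as the closing HAP item in the LEAP guides (Appendix B). The website sections of the control guides refer to the NHS site throughout. This suggests that one item was carried over without adaptation.

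**The case against.** The strongest reply is that these are topic guides for semi-structured interviews, not fixed questionnaires. Refusal is a named research question, and the coding manual is to draw on the research questions. A skilled interviewer could turn item 1 (pathway), item 4 (reasons), item 6 (what might have encouraged them) and item 8 (anything else) towards the decision to decline. In addition, people first express interest and are screened by telephone before they are invited, and the group includes some who declined only randomisation, so items 2 and 3 may partly apply.

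This stands in part. A reader might infer that the pilot cannot collect reasons for refusal, and the documents do not support that. What remains is that the guide itself does not direct the interviewer to the question it exists to serve, and that item 7 has no meaning for anyone in this group.

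Four further inferences are tempting and should not be drawn:
- **That the control interviews are invalid.** Only one item per guide is wrong. The items on participation, the NHS website, and the time, range and difficulty of the HAP measures are sound.
- **That willingness to be randomised goes unexplored.** All four trial-arm guides ask about chance allocation and probe understanding of randomisation. What is missing is narrower: the objections of those who declined. The Research Aims section does not itself name refusal; the support lies in the qualitative objective and Domain 1.
- **That a comparison between arms of how assessment affects website use is lost.** No research question in the three domains asks for one.
- **That naming LEAP reveals the allocation to controls.** The information sheet is not shown, so what controls already know is unknown. Their guides already ask about being allocated by chance to the NHS website.

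**Conclusion.** The point holds as a mismatch between an instrument and its own research question. Appendix D duplicates Appendix E on all eight items, contains no item on why the person declined, and includes three items, and largely a fourth, that do not fit people who never joined. This affects up to 2 of up to 28 interviews, but they are the ones planned for question 2 of Domain 1. Separately, one closing item in each control guide refers to an intervention controls did not receive, in up to 8 interviews.

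The conclusion assumes that the guides would be used as printed; probing could reduce the loss by an amount the documents do not allow one to estimate. The effect stays within the qualitative component: randomisation, the quantitative outcomes and their analysis are unaffected. The Appendix D mismatch should be corrected before interviews begin. The control item is a minor correction to make at the same time.

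**What to change.** 1. Give Appendix D its own items: why the person declined, including any objection to being randomised, and what might have changed the decision. Keep the items on the recruitment pathway, expectations and the reason for agreeing to the interview. Remove those that presuppose leaving, staying or allocation (4, 6 and 7), reword item 2 to ask what first attracted the person, and reword item 8 so that it does not assume participation.
2. Leave Appendix E as it is; its items suit people who withdrew.
3. In the HAP section of both control guides in Appendix C, replace LEAP with the NHS LiveWell website or delete the item.

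The cost is rewriting one short guide, editing one item in two others and, if the ethics committee requires it, submitting the revised guides. Sample size, visits and analysis do not change.
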